## Abstract

**Background:**

Diabetes mellitus (DM) is a major noncommunicable disease with a significant increase in prevalence, especially in low- and middle-income countries. The latest International Diabetes Federation Diabetes Atlas (2025) reports that 11.1% of the adult population (20 to 79 years old) is living with diabetes, with over 4 in 10 unaware of their condition. Early diagnosis and treatment of diabetes reduce the risk and slow the progression of debilitating complications, such as amputation, vision loss, renal failure, cardiovascular disease, dementia, some cancers, and infections like tuberculosis and severe COVID-19. Current screening methods for diabetes are invasive and costly. This has limited their utilization, especially in high-density populations and low- and middle-income countries such as Indonesia. Blood Glucose Evaluation and Monitoring (BGEM) is a machine learning algorithm developed by Actxa to analyze photoplethysmography data from wearable devices for diabetic risk assessment. Its noninvasive and user-friendly nature makes it a strong candidate for fulfilling the need for a diabetes screening or monitoring tool.

**Objective:**

The aim of this study is to collect a large and more diverse dataset for the training of BGEM machine learning models. This dataset is intended to improve the model’s generalizability and to evaluate its performance across different age groups, racial groups, and skin types, with the goal of enhancing accuracy and robustness for diabetes risk assessment and glucose monitoring.

**Methods:**

Adult participants aged 18 years and above, with either a diabetic or a nondiabetic history, who reside in Greater Jakarta Area, Indonesia, were approached for recruitment. Blood glucose was assessed using laboratory blood analysis from capillary or plasma samples after fasting and at 1, 2, and 3 hours after a meal. BGEM data were also collected at each of these time points. Anthropological measurements with a standardized questionnaire on physical activity, demographic information, respondent’s diabetic status, and current medications taken were also collected.

**Results:**

Between June and October 2024, 885 participants were enrolled. Eight photoplethysmography recordings per participant were collected across 4 meal time points using 2 wearable devices in addition to the collection of clinical measurements, blood sampling, and related questionnaires.

**Conclusions:**

This protocol paper outlines the methodology designed for assessing and interpreting participants’ blood sugar profiles, especially on demographic variability, in order to evaluate BGEM, a photoplethysmography-based artificial intelligence model designed to estimate blood glucose levels and diabetic risk. The clinical trial was conducted on Indonesian participants with and without diabetes while considering various influencing factors. This dataset is designed to enable assessment of the model’s performance across diverse racial, risk factors, and skin-type groups, with the aim of making the model more valid and reliable.

## Introduction

Diabetes mellitus (DM) is a major noncommunicable disease that has affected around 500 million people worldwide and continues to rise up to 700 million people globally in 2045 [1]. Other noncommunicable diseases’ death risks have decreased by 20% since the turn of the century; DM, in contrast, has increased by 3% worldwide. The latest International Diabetes Federation Diabetes Atlas (2025) reports that 11.1% of the adult population (20‐79 y) is living with diabetes, with over 4 in 10 unaware of their condition.

Several reports have projected that about 1 in 2 adult patients with diabetes are unaware of their diagnosis [1-3]. Undiagnosed DM has resulted in an increase of cases with complications and elevated the burden of the disease, as younger undiagnosed DM cases have more rapid progression of complications and lower response to general DM treatment. This has been shown to be higher in low- and middle-income countries, where 80% of the DM population lived, thus reflecting the enormous burden of the disease [4,5]. Meanwhile, early diagnosis and treatment of DM reduce the risk and slow the progression of debilitating complications such as amputation, vision loss, renal failure, cardiovascular disease, dementia, some cancers, and infections including tuberculosis and severe COVID-19 [6]. All of the above calls for early screening and frequent monitoring strategies that are both effective and cost-efficient.

Currently available methods to detect DM are hemoglobin A_1c_ (HbA_1c_) level, fasting plasma glucose, 2-hour glucose tolerance test, and random plasma glucose test. All these methods are invasive; they require trained professionals and laboratory equipment to be performed correctly. The American Diabetes Association has recommended DM screening starting at 35 years and every 3 years after, especially for people with obesity, overweight, and one risk factor [7]. In low- and middle-income countries, this is even harder to implement due to the cost and scarce resources of such screening methods [5,6,8].

Indonesia, a middle-income country with a population of 283 million, faces a big challenge in DM management. It was estimated that DM prevalence was 9.49% (2024) and will increase to 16.09% (2045) without any major effective intervention [9]. As in any other low- and middle-income countries, the cost and availability of DM-related testing have prohibited Indonesia from enacting an effective prevention or screening program; therefore, an affordable, effective, and simple screening or monitoring method for DM will be a boon in the national health program.

Photoplethysmography is a noninvasive optical technology that measures light absorbance to assess blood volume changes. It has been widely integrated into wearable devices, such as smartwatches, to monitor heart rate (HR) and other physiological parameters [10]. Emerging research suggests that photoplethysmography data may also be valuable for detecting DM and estimating glucose levels [11-13]. The noninvasive nature, affordability, and convenience of photoplethysmography make it a promising tool for early detection and preventive screening of DM, especially in large and diverse populations, such as in Indonesia. Despite photoplethysmography technology’s potential use in estimating blood glucose and DM prediction, several issues have been reported to influence its performance, such as medication status of subjects [14], motion artifacts [15], and also skin types [16]. This protocol paper will strive to address these issues to improve the reliability (accuracy and robustness) of photoplethysmography-based technology in wearable devices for blood glucose monitoring and DM risk prediction through advanced artificial intelligence (AI) and data analytics.

Blood Glucose Evaluation and Monitoring (BGEM), a machine learning (ML) algorithm developed by Actxa to analyze photoplethysmography data for assessing diabetic risk. It is one of the first ML models deployed in commercial wearable devices. BGEM was trained using data collected from a registered clinical trial (NCT05504096) conducted at KK Women’s and Children’s Hospital in Singapore, involving 500 Singaporean participants. The reported accuracy of BGEM is 84.7% [12]. The model’s performance is sensitive to demographic features, with the inclusion of demographic data significantly enhancing its accuracy [13]. BGEM would benefit from a larger and more diverse training dataset, as the current training data consists primarily of Singaporean participants, predominantly healthy females.

In addition to glycemia prediction, novel methods for diabetic risk assessment and management based on multiple glucose measurements may be developed using BGEM due to its lower cost and noninvasiveness. Glycemic variability, which refers to fluctuations of blood glucose concentration that happen in a day or similar timeframes on different days, has been shown to be associated with microvascular and macrovascular damage in patients with DM [17]. Glycemic variability has been proposed in multiple studies for DM management; however, difficulties in the measurement and consensus on its optimal value, even with recent more widespread use of continuous glucose monitoring, have limited its use in the general population [17,18], despite the general acceptance that it is a promising indicator for DM control.

Here, we present the protocol for a registered clinical trial (NCT06642467) designed to collect a larger and more robust training dataset to enhance BGEM’s performance. This study will collect data to improve current algorithm performance, with an attempt to generalize the diagnostic findings from the previous clinical study to specific groups of participants, with the goal of enhancing accuracy and robustness for glucose monitoring and diabetes risk assessment. The study aims to comprehensively collect photoplethysmography data using 2 different types of wearable devices at multiple time points before and after a breakfast meal. Both capillary and plasma blood samples were collected and subjected to thorough laboratory analysis. Participants from Indonesia were recruited, ensuring a balanced representation in terms of diabetic status (diabetic or nondiabetic) and gender. Additionally, a comprehensive questionnaire was used to gather essential information, capitalizing on the diversity of the training data, including factors such as hypertension, skin type, and other relevant variables, which have been reported to possibly influence either photoplethysmography sensor readings or ML model prediction.

## Methods

### Participant Recruitment

A total number of 885 participants from adults aged 18 years and above were recruited. These participants reside in the Greater Jakarta Area, Indonesia, and were from the diabetic exercise group, from staff and family members of Krida Wacana Christian University (Ukrida), and from its affiliated organizations. Participants were recruited using an online registration provided by the research team. Exclusion criteria were implemented as follows: BMI >37 kg/m^2^, diastolic blood pressure ≥120 mmHg, and systolic blood pressure ≥180 mmHg, wearing a pacemaker, having fever or any other acute critical illness during the data collection, and pregnant female participants. All subjects received an explanation on the study purpose, protocol, and risks, and also signed the informed consent prior to admission to the research study.

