**Figure 1. F1:**
[figure not shown]
A conceptual framework of study design from recruitment, data collection, to discharge for 473 participants who self-acknowledged having diabetes mellitus (DM) and 412 participants who did not (non-DM).

Subsequently, each participant’s photoplethysmography data at the fasting time point (the first time point) were collected using both a smart ring (JC Smart Health Ring 2301B) and a smartwatch (Actxa Spark+Series 2), both provided by Actxa Pte Ltd. Simultaneously, blood samples were obtained from 2 sources: capillary blood for glucose concentration measurement using Accu-Chek (Roche) and plasma blood from the cubital vein for laboratory analysis, as described in a later section.

Participants then consumed a 552-kcal meal set with 79.8 g of carbohydrate content prepared by Ukrida Hospital. This meal was chosen to ensure adequate sustenance and satiety after overnight fasting, as sugary drinks alone may not sufficiently fulfill. The nutritional composition of the meal is detailed in Textbox 1 and Table S1 in Multimedia Appendix 1.

Textbox 1.Nutritional value of the set meal for the subjects, given after subjects fast for a minimum of 8 h and undergo first blood sample collection and photoplethysmography reading from wearables.Energy (kcal): 552.1Water (g): 241.8Protein (g): 19Protein percentage: 13.8Fat (g): 19.3Fat percentage: 31.5Carbohydrate (g): 79.8Carbohydrate percentage: 57.8Dietary fiber (g): 5.2Polyunsaturated fatty acid (g): 1.8Cholesterol (mg): 33Vitamin A (µg): 1396.8Carotene (mg): 0.4Vitamin E (eq.) (mg): 0.8Vitamin B1 (mg): 0Vitamin B2 (mg): 0.1Vitamin B6 (mg): 0.6Total folic acid (µg): 31.8Vitamin C (mg): 10.7Sodium (mg): 1015.5Potassium (mg): 549.4Calcium (mg): 59.2Magnesium (mg): 66.2Phosphorus (mg): 231.5Iron (mg): 2.5Zinc (mg): 1.6

Participants then underwent measurements at the second time point (1 h postprandial), third time point (2 h postprandial), and fourth time point (3 h postprandial). Photoplethysmography data collection followed the same procedure as the first time point using both the smartphone and the smart ring. For blood sample collection and testing, the third time point followed the same procedure as the first time point, with both capillary and plasma blood samples collected and analyzed. At the second and fourth time points, plasma blood collection was omitted, and only capillary blood samples were obtained and tested. Further details are provided in Table 1.

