**Table 1. T1:** Blood glucose metabolism-related data collection from photoplethysmography sensors from 2 wearables, a glucometer, and blood samples based on several time points before and after meal.

Measurements	Smart ring^a^	Smartwatch^b^	Glucose meter^c^	Plasma blood^d^
First time point (fasting state)	Yes	Yes	Yes	Yes
Second time point (1 h postprandial)	Yes	Yes	Yes	No
Third time point (2 h postprandial)	Yes	Yes	Yes	Yes
Fourth time point (3 h postprandial)	Yes	Yes	Yes	No

a JC smart health ring 2301B.

b Actxa Spark + Series 2.

c Roche, ACCU-CHEK guide.

d Full blood count: Sysmex XN-550. Plasma glucose: Roche, Cobas c111 Analyzer. Hemoglobin A_1c_ level: Finecare FIA Meter III Plus.

During the 1-hour intervals at the last 3 time points, while waiting between data and sample collection, participants were asked to complete the International Physical Activity Questionnaire long form, along with questionnaires related to DM and other factors that may affect photoplethysmography reading and BGEM prediction that follows, such as skin type, treatment status, dominant hand, and race (Table 2).

**Table 2. T2:** Baseline study questionnaire and test descriptions collected from the study’s participants.

Questionnaire and test	Description of content	References
Demographic	Five items: age, gender, ethnicity, handedness, an Fitzpatrick skin type	[13]
Diabetic status and history	Six items: family history, status, year diagnosed, medication, gestational diabetes, and drink consumption	[13,20-23]
Relevant medical history	Four items: smoking, hypercholesterolemia, hypertension, and related medication	[13,21-23]
Physical activity	International Physical Activity Questionnaire (IPAQ) long form; 27 items	[24]
Clinical measurements	Four items: weight, height, waist circumference, and blood pressure	[13,20,21,23]
Pre-photoplethysmography measurements questions	Seven items: time of medication, time of meal, meal content, physical activity in 24 h, last, duration, and intensity	[12,25]

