### Statistical Analysis

Demographic data for continuous variables will be presented as mean (SD), and categorical variables will be presented as count (percentage). Univariate analyses will be performed using *t* tests for independent groups for continuous variables and chi-square tests for categorical variables. Discriminations are assessed by plotting the receiver operating characteristic curve and calculating the area under the receiver operating characteristic curve (AUC) or *C* statistic. The accuracy of the prediction model will be analyzed using both Type I and Type II Parkes Error Grids. The sensitivity, specificity, and *F*_1_-score of the BGEM model will also be evaluated and presented to give a clear description of its strength and weakness.

The Parkes Error Grid is used to assess how clinically risky an inaccurate blood glucose reading might be. Each device reading is compared with a reference value and placed into 1 of 5 zones. Zone A means the reading is clinically accurate and would not change treatment. Zone B reflects small errors that might adjust a decision but have little or no impact on outcome. Zone C includes errors likely to affect clinical results. Zone D involves inaccuracies that could lead to clearly risky treatment decisions. Zone E represents dangerous errors that could cause severe or life-threatening consequences if acted upon [27].

The ML model will be trained using Lasso regression, cross-validation, and other ML techniques to find the optimal regularization parameter to ensure that the model generalizes to unseen data. The dataset is initially divided into a training set and a validation set. The training set is used for model development and hyperparameter tuning, while the validation set is reserved for a final, unbiased evaluation of the model’s performance. Analysis will ensure that the model does not overfit to the training data and is able to predict outcomes on new data with confidence. Once the optimal regularization parameter is identified through cross-validation, a final regression model is trained on the entire training set using this optimal regularization parameter value.

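### Diabetes cases are self-acknowledged and partly recruited from a diabetic exercise group, so overall AUC and sensitivity do not transfer to screening for unaware diabetes

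*Protocol article*

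**What the plan says.** Recruitment: participants "were from the diabetic exercise group, from staff and family members of Krida Wacana Christian University (Ukrida") and from affiliated organizations, through online registration (Participant Recruitment).

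Case definition: the Figure 1 caption gives "473 participants who self-acknowledged having diabetes mellitus (DM) and 412 participants who did not (non-DM"). Table 2 records diabetes history by questionnaire: "Six items: family history, status, year diagnosed, medication, gestational diabetes, and drink consumption". Table 3 carries the same 473 forward as the type 2 diabetes proportion.

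Intended use: the Abstract opens with "11.1% of the adult population (20 to 79 years old) is living with diabetes, with over 4 in 10 unaware of their condition". The Introduction adds that "about 1 in 2 adult patients with diabetes are unaware of their diagnosis" and says that the properties of photoplethysmography "make it a promising tool for early detection and preventive screening of DM". The Discussion (Overview) presents the study as a possible basis for management, prevention and screening in Indonesia.

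Analysis: an ROC curve and AUC are planned, and "The sensitivity, specificity, and *F*_1_-score of the BGEM model will also be evaluated" (Statistical Analysis). The condition being discriminated is not named, and no split by awareness, treatment or duration is given.

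Laboratory data: plasma glucose and HbA1c are measured (Table 1, Blood Sample Analysis), but no stated rule uses them to define diabetes. Study Limitations covers the unplanned demographic mix, age over 60 and ethnic composition. It does not mention the spectrum of disease among cases.

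**The concern.** Screening has to find people who do not know they have diabetes. The labelled cases here all know, and one recruitment source is by its name a group for people with diabetes. Known cases may differ from unaware ones in treatment, duration and activity. The model inputs include heart rate, heart rate variability and waveform shape (Photoplethysmography Data Feature Extraction), and the Introduction itself lists medication among the influences on photoplethysmography performance. A classifier could therefore partly separate treated or exercising people from the rest. This is a question of case spectrum, and it would remain if every self-reported label were correct.

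At stake is what the study may conclude. A single overall AUC or sensitivity could be read as evidence for screening although the group that screening targets contributes few cases or none.

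**Working it through.** **The plan's own figures.** For a Bland-Altman limit of agreement, the 95% CI half-width is 1.96 × √(3/n) × SD. At n = 200 this is 1.96 × √0.015 = 0.240 × SD, as stated in Study Design. Dropout: 800 / 0.90 = 889, against the stated figure of about 890. Counts: 473 + 412 = 885, and 473/885 = 53.4%. The sample size is not in question. It was set for measurement error in four sex-by-diabetes groups, not for AUC or sensitivity.

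**If cases are the self-acknowledged group.** Unaware cases on the case side number 0 of 473. Any unaware person among the 412 counts as non-diabetic.

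**If cases are defined by laboratory values.** Inputs from the article:
- prevalence p: "It was estimated that DM prevalence was 9.49% (2024") for Indonesia, and 11.1% of adults from the global figure;
- unaware share u: 0.4 (the article says over 4 in 10) and 0.5 (about 1 in 2).

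Assumption: the 412 resemble the general population apart from not acknowledging diabetes. The unaware share among them is then p × u / (1 − p × (1 − u)):
- p = 0.0949, u = 0.4: 0.03796 / 0.94306 = 4.0%, or 16.6 of 412
- p = 0.0949, u = 0.5: 0.04745 / 0.95255 = 5.0%, or 20.5
- p = 0.111, u = 0.4: 0.0444 / 0.9334 = 4.8%, or 19.6
- p = 0.111, u = 0.5: 0.0555 / 0.9445 = 5.9%, or 24.2

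As a share of all cases this is 16.6 / (473 + 16.6) = 3.4% to 24.2 / (473 + 24.2) = 4.9%.

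**How firm is that?** If the upper count were doubled to 48, the share would be 48 / (473 + 48) = 9.2%. Some self-acknowledged participants might not meet a laboratory definition. With 24 unaware cases, known cases would lose their majority only if more than 473 − 24 = 449 of the 473 (95%) failed to meet it.

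**What a pooled sensitivity would show.** For illustration, take 84.7% in known cases (borrowed from the accuracy reported for the existing model) and 50% in unaware cases (assumed). With 17 unaware cases: (473 × 0.847 + 17 × 0.5) / 490 = 83.5%. With 24: (473 × 0.847 + 24 × 0.5) / 497 = 83.0%. Poor performance in unaware cases would move the overall figure by less than 2 points. This shows how insensitive the pooled figure is. It does not predict how the model will perform.

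**Precision in the group of interest.** The half-width is 1.96 × √(s(1 − s)/m). At s = 0.70 and m = 16.6 it is ±22 points; at s = 0.90 and m = 24.2 it is ±12 points. For the 473 known cases the same sensitivities give about ±4 and ±3 points.

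**The case against.** The strongest reply is that the endpoint behind the AUC is unnamed. The regression target is finger-prick glucose, diabetes status is listed among the model's input features, and accuracy is judged by Parkes error grids. If the AUC refers to a glucose or HbA1c threshold, undiagnosed people among the 412 could count as cases. This stands as a limit on the wording: the absence of unaware cases is certain only under the self-report grouping. Under a laboratory threshold, known cases would still probably dominate.

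Second, the study mainly gathers training data for risk assessment and glucose monitoring, and balancing by diabetes status is reasonable for that. This also stands in part. The Parkes grid and agreement analyses are less affected, and screening is one hoped-for later use. But diabetes risk assessment is in the stated objective, and screening is part of the rationale.

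Third, subgroup detail may be in a fuller protocol or analysis plan, and the Discussion promises to study factors that influence accuracy. It names anthropometry, HbA1c, hematocrit and other blood parameters, not treatment, duration or recruitment source. The point does not depend on missing subgroup detail. It rests on what the article does fix: the source and definition of the cases and the screening rationale, with limitations that omit disease spectrum.

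A reader might go further and infer that the cases are long-standing and treated, and that the reported performance is therefore inflated. The article does not support this. It gives no treated share, no duration and no share from the exercise group. It says that medication matters but not in which direction, and treated disease might be harder to detect by photoplethysmography.

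**Conclusion.** The concern holds as a limit on what can be concluded. Under the self-report grouping, none of the 473 labelled cases is unaware. Under a laboratory definition, about 17 to 24 unaware cases would be expected, roughly 3% to 5% of all cases, if the 412 resemble the general population and the self-acknowledged participants remain cases. Either way, the overall AUC, sensitivity, specificity and F1 would chiefly describe known diabetes and do not transfer to screening. The direction and size of any bias cannot be derived from the article, so no inflation figure should be attached. This does not invalidate the dataset for training or for glucose monitoring. It is a worthwhile, inexpensive improvement to analysis and reporting.

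**What to change.** In Statistical Analysis:
1. Name the condition behind the AUC, and label the overall AUC and sensitivity as discrimination of known diabetes.
2. Use the HbA1c and plasma glucose already measured to identify participants without self-acknowledged diabetes who meet a pre-specified laboratory definition. Report performance for them separately, with confidence intervals.
3. Among known cases, report AUC and sensitivity by use of glucose-lowering drugs and by years since diagnosis, adjusted for age and physical activity score. State that this is a proxy only, because recently diagnosed or untreated participants are still aware of their disease. Leave out exercise-group participants as a sensitivity analysis only if recruitment source was recorded per person; Table 2 does not list it.
4. Base any screening statement on item 2, supported by item 3, and add disease spectrum to Study Limitations.

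No new recruitment or measurement is needed for items 1, 2 and 4, nor for the strata in item 3, which use questionnaire items in Table 2. The cost is wide intervals in small strata: about ±12 to ±22 points for 17 to 24 laboratory-detected cases at an assumed sensitivity of 70% to 90%. The data may support no firm screening statement, and the report should then say so.
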